## **Hand washing with soap and nail clipping: effect on intestinal parasitic infection in school-aged children: a factorial randomised controlled trial**

The study design shall be a factorial randomised controlled trial, whereby different intervention packages will be randomised among households with children recruited for the survey.

A total of 216 households with at least one school-aged child (aged 6-15) will be randomly selected by systematic random sampling method. Selection of households will be made based on the DHSS (Demographic Health Surveillance Site) baseline census. Hand-washing with soap intervention will be implemented at household level, using selected child (aged 6-15) within the household as study unit. If there is more than one child in the age group per randomised household two children will be selected by simple lottery method and will be included in the trial. Reported age of a child will be cross-checked using school- records, baptism certificates, local calendars and birth certificates (if available).

Each intervention and control group will have a fixed number of participants, and will be subjected to only one of the study interventions. Children in each group will be followed-up for 6 months and parasitological and haemoglobin data will be collected following intervention. Different intervention packages shall be evaluated separately (the primary comparisons are the main effects), in combination and also against the control groups (groups with standard habits and practices).

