### Requirement of parasite free children

Prior to random allocation to the intervention and control arms and following acquisition signed informed consent, children will be screened for intestinal parasitosis. Children screened positive for intestinal parasitic infections will be treated using standard treatment regimen. Parasite negative children in the respective households will be randomly assigned into different intervention and control groups and randomisation will be by sealed envelope method.

[figure not shown]

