**Concealment and blinding**

Children and household assignment sequence will be concealed. Researchers assessing the outcomes will be blinded to group assignments. Lab personnel will be blinded to group assignment and to the assessment outcomes. Participating children and their families can be aware of the intervention they receive but will be blinded for the study hypothesis and the intervention(s) given to the other groups. The study will be explained as an assessment of intestinal parasitosis, anaemia and malnutrition among school-aged children, while the principal purpose of assessing the impact of hand washing and nail clipping will be concealed.

[figure not shown]

**Specific Aim I: Evaluate the impact of hand washing with soap and hand nail clipping on parasite re-infection rates, intensity and self-reported illness.**

**Objective and Rationale:** Effective preventive tools serve in decreasing the burden of entroparasite infections. Periodic drug administration, proper hygiene and sanitation are known to keep the levels of infection below those associated with morbidity, and hence improve the health and development of individuals, especially of children. The fact that parasitic infections impair children's growth and development is of a public health concern.

Although treatment reduces both transmission and infection rates of intestinal parasitic infections, whether this intervention measure is sustainable solution is not clear as rapid re-infection usually occurs. There is also emerging evidence that concurrent worm infections may have impacts on child development and nutritional status. The potential impacts of hand hygiene promotion activities on intestinal parasitosis and illness among children merit extensive investigation.

**Methodology:** Parasitological analysis will be carried out and children diagnosed positive for intestinal parasitic infections will be treated and recruited for the study. A detailed household listing and identification of households with children under investigation will be carried out. Upcoming allocation sequence will be concealed from participants and field workers, and households will be randomized to receive either: (a) hand washing with soap; or (b) hand nail clipping; or (c) both interventions; or (d) neither of the intervention packages. Children assigned to intervention arms of hand washing with soap and finger nail clipping will be provided with soap and nail clippers, respectively.

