## **Data Processing and Analysis**

Data will be entered and processed on an appropriate software and will be analysed using appropriate statistical analysis methods. Effectiveness of interventions will be assessed using regression models by odds ratio with help of SPSS version 16 software. Effectiveness of an intervention will be estimated based on a comparison of all individuals allocated to receive a particular intervention package versus those allocated not to receive the intervention. Infection intensity differences between intervention and control arms will be analysed by arithmetic mean differences for the egg counts using the independent-samples t-test. Participants will be analysed according to the group to which they were randomized. Base-line demographic and hygiene information will be obtained using structured questionnaire. Questionnaires will be coded by investigator and statistician, and data entry will be done using an appropriate statistical software. Statistical significance will be tested with  $\chi^2$  and shall be set at  $p < 0.05$ .

**Problems and pitfalls:** The study is expected to have limitations arising from the study design to be followed, the process of data collection and nature of the study respondents. As behavioural trials are difficult to be blinded, systematic error is expected to occur due to the lack of blinding. An attempt to reduce this effect will be made by masking field workers to the identity of the assigned interventions and the outcome of interest. Field workers will check the presence of soap for hand-washing in the households other than those assigned to hand-washing intervention, and nail clippers in households other than assigned to the intervention during their weekly visits in an attempt to check for contamination.

Loss-to-follow-up will be reduced, and compliance during follow-up will be enhanced by recruiting children and households who are interested and reliable in to the selection process, and by arranging frequent contacts with individual members of the families.

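### Households are allocated and up to two siblings each are followed, but the named t-test and chi-square test treat children as independent, and no household term is stated for the odds-ratio regression

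*Protocol*

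**What the plan says.** **Allocation.** The protocol's opening section says that "different intervention packages will be randomised among households with children recruited for the survey". Specific Aim I, Methodology (under Concealment and blinding) agrees: "households will be randomized to receive either: (a) hand washing with soap; or (b) hand nail clipping; or (c) both interventions", or neither. The table under Sample size determination places 216 households in four cells of 54. One section reads differently. Requirement of parasite free children says: "Parasite negative children in the respective households will be randomly assigned into different intervention and control groups".

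**Who contributes outcomes.** The opening section says: "Hand-washing with soap intervention will be implemented at household level, using selected child (aged 6-15) within the household as study unit". It continues: "If there is more than one child in the age group per randomised household two children will be selected by simple lottery method", and both enter the trial. A household therefore supplies one or two children.

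**Analysis.** Data Processing and Analysis takes the individual as the unit of comparison. Effectiveness is estimated by regression giving odds ratios, with the model not specified further. Infection intensity is to be analysed by "arithmetic mean differences for the egg counts using the independent-samples t-test". The section also states: "Statistical significance will be tested with" a chi-square statistic, at p < 0.05. No section mentions household correlation, a household effect or robust standard errors.

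**The concern.** The independent-samples t-test and the ordinary chi-square test both assume independent observations. Two children from one household are not independent. They receive the same allocation and share the household's soap, water and surroundings. The protocol itself supplies a mechanism: its Hand Washing With Soap section explains that contaminated hands dipped into stored household water can pass pathogens to other family members.

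When siblings share an allocation and their outcomes are positively correlated, an analysis by child counts more information than the data hold. Standard errors come out too small and the test rejects too often. This reaches both primary outcomes (re-infection and infection intensity), the anaemia outcome, and both main effects, which the protocol names as its primary comparisons.

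**Working it through.** **1. The plan's own figure.** Sample size determination uses 72.2% prevalence, a 20-point reduction (to 52.2%), 80% power and a 5% level. With the unpooled formula given there and a multiplier of 7.85 for these settings:

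n = (0.722 × 0.278 + 0.522 × 0.478) / 0.20² × 7.85 = 0.4502 / 0.04 × 7.85 = 88.4

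This matches the stated 88, rounded to 90 **households** per group. Adding 20% gives 180 + 36 = 216 households, also as stated.

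**2. Design effect.** Let s be the share of households with two children. Per household, the mean of m is 1 + s and the mean of m² is 1 + 3s, so

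DE = 1 + ICC × (Σm²/Σm − 1) = 1 + ICC × 2s/(1 + s)

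The multiplier of the ICC is 0.667 at s = 0.5 and 1 at s = 1. Under household allocation siblings stay together on both factors, so the same DE applies to both main effects.

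**3. True type I error.** For a nominal two-sided 5% test (the protocol does not state sidedness), this is 2 × [1 − Φ(1.96/√DE)]. The protocol gives neither the ICC nor s, so both are assumed ranges.

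| ICC | DE, s = 0.5 | Type I error | DE, s = 1 | Type I error |
|---|---|---|---|---|
| 0.1 | 1.07 | 5.8% | 1.10 | 6.2% |
| 0.2 | 1.13 | 6.6% | 1.20 | 7.4% |
| 0.3 | 1.20 | 7.4% | 1.30 | 8.6% |
| 0.5 | 1.33 | 9.0% | 1.50 | 11.0% |

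The correct standard error is √DE times the naive one: 1.03 times at DE 1.07 and 1.22 times at DE 1.5.

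**4. Simulation check.** Beta-binomial data were simulated with 108 households per arm, two children in each, 60% infected in both arms and 40,000 runs. The ordinary chi-square test rejected in 6.3%, 7.2%, 8.7% and 11.1% of runs at ICC 0.1, 0.2, 0.3 and 0.5, in line with the formula. This check covers the binary outcome. For the t-test the same formula applies, with the ICC of egg counts, which may differ.

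**5. Power.** The effective number per group at 90 households is 90 × (1 + s)/DE. At s = 1 and ICC 0.5 this is 180/1.5 = 120, giving about 90% power. At s = 0.25 and ICC 0.5 it is 112.5/1.2 = 93.8, giving about 81%. Over s from 25% to 100% and ICC from 0.05 to 0.5, power after correction is 81% to 97%.

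**The case against.** **A reader might infer that every planned analysis ignores the household.** The protocol does not support that. A GEE or mixed logistic model is also a regression giving odds ratios, and an SAP, which is not shown, could specify one. A chi-square statistic could even be a Wald test from such a model. This stands for the regression. It does not rescue the t-test, which is named outright for a primary outcome, or the chi-square test, which is named without qualification and would ordinarily be read as the plain test. An SAP using clustered methods would have to override both.

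**The unit of allocation is not stated consistently.** Requirement of parasite free children has children assigned, and nail clipping is delivered child by child with a coded clipper for each. If siblings were split between arms, the design effect above would not apply and naive tests would tend to be conservative. This stands as a condition on the direction of the error. Household allocation remains the better reading: the design statement, Specific Aim I and the sample-size table all use it, and soap is supplied to the household.

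**The effect is modest.** Clusters of at most two cap the design effect at 1 + ICC. The 11% figure needs both assumptions at their upper end, and a wider grid (ICC from 0.05, 25% two-child households) starts at about 5.2%. This stands as a limit on size.

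**A reader might also infer that the trial is underpowered.** It is not, on this ground: the sample size counts households, and a second child can only add information.

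**Conclusion.** Wrong as written. Under household allocation with up to two siblings, the t-test and the ordinary chi-square test give p-values that are too small and intervals that are too narrow for both main effects, and nothing stated for the regression prevents the same fault there. On an assumed ICC of 0.1 to 0.5 and 50% to 100% two-child households, the design effect is 1.07 to 1.5 and the true type I error about 5.8% to 11%. The direction rests on positive sibling correlation and on siblings sharing an allocation; the size rests on the two assumed ranges. The fault lies in the analysis and not in the sample size, and no bias in the point estimates is claimed.

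**What to change.** - State the household as the unit of allocation, and reconcile Requirement of parasite free children with the opening section and Specific Aim I.
- For re-infection and anaemia, keep the odds ratio. Estimate it by logistic GEE with household as the cluster and robust standard errors, and take the p-value from that model in place of the plain chi-square test.
- For infection intensity, keep the arithmetic mean difference in egg counts. Use household-clustered robust standard errors in place of the independent-samples t-test.
- State that all p-values and intervals come from these analyses.

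Clustering does not require a change of effect measure, so a count model or a log-binomial model is not needed on this ground. The cost is analysis wording and slightly wider intervals, with no extra participants or data.

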### **Sample size determination**

Using the formula for ‘comparison of proportion of successes’ and assuming equal groups; based on data collected previously in the study area on prevalence of intestinal parasitosis among the age-group (72.2% -data from previous prevalence study in the area) and assuming prevalence reduction of 20%; taking a power of 80% and assuming a significance level of 0.05; the sample size per group (intervention and control) will be 90 households.

$$n = \frac{\left\{ \begin{array}{c} \text{success x failure} \\ \text{on treatment A} \end{array} \right\} + \left\{ \begin{array}{c} \text{success x failure} \\ \text{on treatment B} \end{array} \right\}}{(\text{success on A} - \text{success on B})^2} \times \text{‘magic number’}$$

Sample size = 88 (90); 90 households in intervention and 90 household in the control arm (n=180). Considering 20% loss-to-follow up = 180 + 36 = 216 households.

|                             |     | Nail clipping (NC) |     |       |
|-----------------------------|-----|--------------------|-----|-------|
|                             |     | Yes                | No  | Total |
| Hand washing with soap (HW) | Yes | 54                 | 54  | 108   |
|                             | No  | 54                 | 54  | 108   |
|                             |     | 108                | 108 | 216   |

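### The 20% loss allowance is added to 180 instead of being taken off the number enrolled, so 216 households leave about 86 per arm, not 90

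*Protocol*

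**What the plan says.** The Protocol, under Sample size determination, compares two proportions "assuming equal groups". The inputs are a control prevalence of "72.2% -data from previous prevalence study in the area", an effect given as "assuming prevalence reduction of 20" per cent, and the error rates in "taking a power of 80% and assuming a significance level of 0.05". The result is "Sample size = 88 (90); 90 households in intervention and 90 household in the control arm (n=180").

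The allowance for attrition follows at once: "Considering 20% loss-to-follow up = 180 + 36 = 216 households". The factorial table in the same section spreads this total over four cells of 54, which makes 108 households on each side of either factor. The opening design section carries the figure forward ("A total of 216 households with at least one school-aged child (aged 6-15) will be randomly selected") and says that "the primary comparisons are the main effects". The arms that the 90 refers to are therefore the 108-household margins, not the cells.

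**The concern.** A loss allowance should make the number enrolled, less the expected losses, equal the number the calculation requires. The expected loss is a share of those enrolled, so the required number has to be divided by one minus the loss rate. The Protocol multiplies by one plus the loss rate. With a 20% rate the two steps do not cancel, because 1.2 × 0.8 = 0.96. The plan ends 4% short of its own requirement at exactly the attrition it says it has planned for.

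What is at stake is the accuracy of a stated figure. Readers will use the 20% to judge whether the attrition observed stayed within what the design allowed. A loss of 18% to 20% would look covered, although the target of 90 per arm is already missed above 16.7%.

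**Working it through.** **Inputs, all from Sample size determination.** Control prevalence 72.2%; reduction of 20%; power 80%; significance level 0.05; equal groups; 90 per arm (180) before loss; 20% loss. Two readings are inferred because they reproduce the stated 88: a two-sided test, and a reduction of 20 percentage points (72.2% to 52.2%).

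**1. Reproducing the plan's figure.** The Protocol's formula is

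n per arm = [p₁(1 − p₁) + p₂(1 − p₂)] / (p₁ − p₂)² × (1.960 + 0.842)²

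- p₁(1 − p₁) = 0.722 × 0.278 = 0.2007
- p₂(1 − p₂) = 0.522 × 0.478 = 0.2495
- sum = 0.4502; divided by 0.20² = 0.04 this is 11.256
- × 7.849 = **88.3**, which matches the stated 88

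The other readings do not match. A one-sided test gives 70 on this formula. A relative reduction of 20% (to 57.8%) gives 167.

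**2. The loss step as printed.** 180 + 0.20 × 180 = 180 + 36 = 216. This is 180 × 1.2.

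**3. What 216 leaves after 20% loss.**

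- 216 × 0.80 = 172.8 households, or 86.4 per arm
- shortfall against 180: 7.2 households
- shortfall against 176 (2 × 88): 3.2 households

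**4. The loss that 216 tolerates.**

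- to retain 180: 1 − 180/216 = 16.7%
- to retain 176: 1 − 176/216 = 18.5%

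**5. The total that 20% loss would need.**

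- from 180: 180/0.80 = 225
- from 176: 176/0.80 = 220
- with four equal cells: 90/0.80 = 112.5 per margin, so 57 per cell and 228 in total

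**6. Power.** On the same unpooled formula, power = Φ(0.20/√(0.4502/n) − 1.960). The pooled-variance version is shown beside it.

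| Households per arm | Unpooled | Pooled |
|---|---|---|
| 90 | 80.7% | 79.5% |
| 88 | 79.8% | 78.6% |
| 86.4 | 79.1% | 77.9% |
| 86 | 78.9% | 77.7% |

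The Protocol's 20% loss therefore costs 80.7 − 79.1 = 1.6 points of power relative to 90 per arm, and leaves the design about 0.9 points under the 80% target.

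**The case against.** Nobody can dispute the sum, so the case on the other side is about its weight.

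- **The text does not expressly promise 90 households per arm after loss.** It could be read as simply adding 20% of the required number. But the 20% is labelled as loss to follow-up, and an allowance for loss has no purpose except to protect the required number. This point does not stand.
- **The fair comparison is with 88, since 90 is a rounding.** From 88 the corrected total is 220, so 216 is under 2% short, and power is about 1 point below target. This stands as a statement of size. It does not rescue the sentence, because 86.4 is below 88 as well.
- **Households with more than one eligible child contribute two.** This adds information. If a fraction f of households has two children and their outcomes correlate at ρ, the effective number is about 172.8 × [1 + f(1 − ρ)/(1 + ρ)]. The Protocol gives neither f nor ρ. To get back to 180, f would have to be about 6% at an assumed ρ of 0.2, 12.5% at 0.5, and 37.5% at 0.8. The true power at 20% loss may therefore exceed 79%. However, the calculation counts households and does not offer the second child as a reserve, so the stated loss figure remains wrong.
- **The factorial design uses all 216 for each factor.** It does, but the 90 per arm already refers to the 108-household margins, so there is no further margin to draw on.

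**Conclusion.** The statement is wrong as written. The figures of 216 households, 20% loss and 90 per arm cannot all hold: 216 covers 16.7% loss, and at 20% about 86 per arm remain. The consequence is minor, at about 7 households out of 180 and 1.6 points of power on the Protocol's formula, and it does not threaten the trial's conclusions.

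The household counts need no assumption beyond reading 20% as a share of those enrolled; the per-arm figure also takes losses as equal in the two arms. The power figures rest in addition on a two-sided 5% test, one observation per household, and the inferred reading of 72.2% versus 52.2%.

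**What to change.** Keep 216 and replace the loss sentence under Sample size determination with wording such as:

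*The 216 households allow for 16.7% loss to follow-up while retaining 90 per arm. At 20% loss about 86 per arm remain, giving about 79% power for 72.2% versus 52.2% (two-sided 5%).*

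The sponsor should confirm that the 20% reduction is meant in percentage points before 52.2% is written in, since the Protocol does not say so.

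The cost is one sentence and a slightly less favourable figure. Enrolment, the factorial table, randomisation and analysis are unchanged. If the sponsor would rather keep the 20% claim, the total becomes 225 by division, or 228 to fill four equal cells of 57. The factorial table and the total in the opening design section would then have to change too. For a gap this small, correcting the sentence is enough.

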### Requirement of parasite free children

Prior to random allocation to the intervention and control arms and following acquisition signed informed consent, children will be screened for intestinal parasitosis. Children screened positive for intestinal parasitic infections will be treated using standard treatment regimen. Parasite negative children in the respective households will be randomly assigned into different intervention and control groups and randomisation will be by sealed envelope method.

[figure not shown]

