### **Hand Washing With Soap**

High prevalence rates of intestinal parasites transmitted through faecal-oral route demonstrates the role played by unhygienic hands in transferring fecal particles from one host to another. Based on our preliminary survey, more than 89% of the children does not use soaps during hand washing and about 41% never wash their hands after defecation. These inadequate hand hygiene practices may transfer pathogens through direct interpersonal contact, contact with inanimate objects and surfaces, and during food preparations. Furthermore, in such setting, where the households store water they use for cooking and drinking in the house, dipping contaminated hands into storage containers can also transfer pathogens to other family members.

Hand-based transmission of pathogens is so ubiquitous that hand washing with soap has been argued to be the best intervention to prevent diarrhoea, and the most cost-effective option for prevention of morbidity and mortality in children.

Most people, especially children, do not wash their hands with soap at important times, such as after using toilet and before eating. The quantity and proximity of water available to households have been demonstrated to correlate with frequency of hand washing. Unfortunately, large proportion of people in developing countries do not have household-level access to piped water, which presents a formidable challenge to increase rates of hand washing with soap and water in such communities.

**Methodology:** Small bars of plain soap will be provided to each household with child in the hand washing with soap intervention and will be replenished as necessary. Children and family members in the respective group will be encouraged to wash their hands with water and soap before meals, after defecation, after playing on the ground and touching animals, before and after preparing food (mothers) and when ever their hands get unclean. Brief clarifications will be given on the clinical importance of intestinal parasitic infections and methods of prevention; proper hand washing procedures will be demonstrated during the commencement of the study and at every visit.

**Training:** Field workers will be trained for two days on the proper hand-washing with soap and nail clipping techniques, the purpose and procedures of the visits, supervisory activities, fellow-up, data collection, and reporting.

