#### **2.1. Procedure of nail clipping**

- Cutting fingernails is easy. Just make sure you have a nice, sharp (**and above all safe**) nail cutter and a wastebasket to collect the nails
- Cut the nails straight across until they no longer extend over the finger, so that they don't show any white
- Follow the shape of the fingertip when trimming finger nails
- Do not cut the nails uneven, this may cause nails to split and crack and hence accumulate dirt and pathogens
- Look the nails over to ensure that they are all of the same length and shape, and also that they're smooth and not uneven or pointy. Keep clipping and filing until they all look the same and are smooth. Once they are, you're done!

**Control condition:** Control households will be provided with a regular monthly supply of sugar in an effort to preserve willingness to participate, but they will be given no products that would be expected to affect their hand-washing and nail clipping behaviours. They will be neither encouraged nor discouraged for hand-washing and nail clipping. Control households will be visited at equal frequency with the intervention households. Control

households will also frequently checked for the presence of soap for hand-washing and nail clippers during the weekly visits to check for contamination.

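### The allocation passage assigns children where the rest of the protocol randomises households; read literally it lets siblings fall in different arms and share household soap

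*Protocol*

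**What the plan says.** Two units of randomisation appear in the protocol.

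- **Child.** *Requirement of parasite free children*: "Parasite negative children in the respective households will be randomly assigned into different intervention and control groups". The same sentence names sealed envelopes as the method, and it is the only place where they are mentioned.
- **Household.** Opening section: "different intervention packages will be randomised among households with children recruited for the survey". Specific Aim I, Methodology: "households will be randomized to receive either" one of four packages. *Sample size determination* counts households: 90 per arm, 216 in total, 54 in each cell of the two-by-two table.

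Three further statements bear on what happens if the child is used.

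- Two children may come from one home: "If there is more than one child in the age group per randomised household two children will be selected by simple lottery method" (opening section).
- Hand washing is a household intervention: "Hand-washing with soap intervention will be implemented at household level" (opening section). Under *Hand Washing With Soap*, "Small bars of plain soap will be provided to each household with child in the hand washing with soap intervention", and "Children and family members in the respective group will be encouraged to wash their hands with water and soap".
- The control condition, described after the nail-clipping procedure, is written for households: "they will be given no products that would be expected to affect their hand-washing and nail clipping behaviours".

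No sentence says that two enrolled children from one household receive the same allocation.

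**The concern.** The unit of randomisation is a protocol-level design element, and here the sentence that names the allocation method uses a different unit from the rest of the document. Where a household has one enrolled child, the two readings coincide. Where it has two, they do not. An envelope per child can place one sibling in a hand-washing cell and the other in a cell without it.

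The second child would then live with trial-supplied soap and weekly promotion directed at the whole family, yet be analysed as not having received hand washing. That pulls the hand-washing main effect, one of the two primary comparisons, towards no effect. It also disturbs other parts of the plan:

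- A split household belongs to two cells, so the 54-household cells are no longer defined.
- It cannot meet the description of a control household.
- The weekly check for soap in households not assigned to hand washing has no clear meaning there.
- The family would see an intervention given to another group, which the blinding section seeks to avoid.

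Nail clipping is less exposed, because each clipper is coded to a child and kept by the field workers.

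**Working it through.** **1. The plan's own figure and its unit.** Inputs from *Sample size determination*: prevalence 72.2%, reduction of 20% (which reproduces only as 20 percentage points, to 52.2%), power 80%, significance level 0.05. With the multiplier 7.85 for a two-sided test:

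n = (0.722 × 0.278 + 0.522 × 0.478) / 0.20² × 7.85 = 0.4502 / 0.04 × 7.85 = 88.4.

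This matches the stated 88, rounded to 90. The protocol calls these households, and 180 + 36 = 216 is also in households. Household randomisation therefore leaves the sample size as it stands.

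**2. How often siblings would be split.** Assume independent, equal allocation of each child to four cells.

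- Same level of hand washing: 1/2, so 50% of pairs differ on hand washing.
- Same cell: 1/4, so 75% of pairs differ on arm.

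**3. Dilution of the hand-washing contrast.** The protocol gives neither of two quantities that are needed, so they are assumptions here:

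- f, the share of children who have an enrolled sibling;
- c, the share of the soap effect passed on to a no-soap child whose sibling has soap.

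Of the no-soap children, a fraction f/2 have a sibling with soap, and each of these receives c × 20 points of benefit. The children allocated to soap are taken to get the full effect. The observed difference is then

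20 × (1 − f × c / 2) points.

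| f | c | Difference (points) |
|---|---|---|
| 0.5 | 0.25 | 20 × (1 − 0.0625) = 18.8 |
| 0.5 | 0.5 | 20 × (1 − 0.125) = 17.5 |
| 0.5 | 1 | 20 × (1 − 0.25) = 15.0 |
| 0.7 | 1 | 20 × (1 − 0.35) = 13.0 |
| 0.9 | 1 | 20 × (1 − 0.45) = 11.0 |

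**4. Why no single power figure follows.** Power depends on the number of children as well as on the dilution. If a share f of children have an enrolled sibling, 180 households hold 180 / (1 − f/2) children: 240, 277 and 327 for f = 0.5, 0.7 and 0.9, or about 120, 138 and 164 per arm. Take the unpooled two-sided z-test, power = Φ(d/SE − 1.96), with SE² = [p₁(1 − p₁) + p₂(1 − p₂)]/n, p₂ = 0.522 and p₁ = 0.522 + d. It gives 81% for 20 points at 90 per arm. With dilution and the child counts above:

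| f | Children per arm | Power, c = 1 | Power, c = 0.5 |
|---|---|---|---|
| 0.5 | 120 | 67% | 81% |
| 0.7 | 138 | 60% | 81% |
| 0.9 | 164 | 53% | 83% |

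These values ignore correlation between siblings. They show how far the answer moves with the assumptions and are not estimates for this trial.

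**The case against.** The best case against the point is that the protocol already settles the unit. The opening section randomises among households and selects children within a randomised household. The sample size, Specific Aim I, the control condition and the contamination checks all speak of households. The sentence at issue stands under a heading about parasite-free children. Its subject may be who is eligible, with the reference to the respective households pointing back to the allocated unit. It does not say one envelope per child. Figures that are not reproduced in the available text might show the unit as well.

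Much of this stands: household randomisation is the likelier intention. It does not remove the conflict. The sentence says that children are assigned, it alone names the envelopes, and the concealment paragraph mentions both children and households. Staff preparing envelopes could follow either unit and be within the text.

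Two stronger readings should be resisted. A reader might infer that siblings will be split; the documents support only that they can be. A reader might also hold 90 per arm fixed, apply the full-sharing dilutions to 15, 13 and 11 points, and conclude that power falls from 81% to 55%, 43% or 32%. That treats 90 households as 90 children while assuming that many households supply two, and it takes complete sharing of the effect as given. With consistent counts the same assumptions give 67%, 60% and 53%, and with half sharing power is about the planned 81%.

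**Conclusion.** The inconsistency is real and should be reconciled before envelopes are prepared, because contamination created by child-level allocation cannot be removed in the analysis. The direction of the bias is clear: towards no effect on hand washing.

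Its size is not determined by the protocol. It is zero if envelopes are in fact issued per household. If they are issued per child, the 20-point difference becomes 20 × (1 − f × c / 2), for example 18.8 points at f = 0.5 and c = 0.25, or 11 points at f = 0.9 and c = 1. This rests on independent equal allocation and on assumed values of f and c. The documents do not support a specific loss of power, or a claim that the trial intends to randomise individual children.

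**What to change.** Amend *Requirement of parasite free children* along these lines: the household is the unit of randomisation; one sealed envelope per household assigns it to one of the four cells (54 households each); and all enrolled children of that household who have been screened parasite-negative take its allocation.

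The restriction to children screened negative is needed. A rule binding every enrolled child in a household with at least one negative child could admit a sibling who is still positive. That would conflict with the requirement in this section and with the repeat screening described under Specific Aim I.

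Use the household as the allocation unit wherever assignment is described, including the concealment paragraph, and state that the analysis accounts for clustering of children within households.

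The cost is a short text amendment before allocation starts. The sample size is already counted in households, so 216 stands and no participants are added.
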